**Methods:**

Our prospective monocentric study will involve three visits (14–18, 24–28, and 34–38 weeks of pregnancy) and include nulliparous women older than 18 years, with a normal pregnancy and a body mass index (BMI) lower than 35 kg.m^− 2^. Each visit will consist of a clinical pelvic floor assessment (using the Pelvic Organ Prolapse Quantification system), an ultrasound perineal measure of the anteroposterior hiatal diameter and SWE assessment of the *levator ani* and the external anal sphincter muscles (at rest, during the Valsalva maneuver and during pelvic floor contraction), and SWE assessment of both the *biceps brachii* and the *gastrocnemius medialis* (at rest, extension and contraction). We will collect data about the mode of delivery and the occurrence of perineal tears. We will investigate changes in continuous variables collected using the Friedman test. We will look for an association between the elastic properties of the *levator ani* muscle and clinical / ultrasound measures using a Spearman test at each trimester. We will investigate the association between the elastic properties of the pelvic floor muscles and perineal tear occurrence using a multivariate analysis with logistic regression.

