In accordance with animal experimentation, we hypothesize that there are changes in elastic properties of women’s pelvic floor through pregnancy and that SWE is relevant to follow these changes [9, 10]. They might be specific to pelvic floor muscles without, or less, significant changes for peripheral muscles such as *biceps brachii* or *gastrocnemius medialis*. Finally, the hypothetical changes in elastic properties of women’s pelvic floor may be associated with their intrinsic risk of perineal trauma at childbirth. Indeed, during vaginal delivery, a major strain is applied to pelvic floor muscles which are stretched up to 3 times their initial length [5, 16]. Thus, intrinsic elastic properties of pelvic floor muscles may be associated with their ability to support this strain without being damaged.

Our main objective is to describe the changes in the elastic properties of the pelvic floor muscles (*levator ani,* external anal sphincter) during human pregnancy using shear wave elastography (SWE) technology. The secondary objectives are as follows: i) to look for specific changes of the pelvic floor muscles compared to peripheral muscles; ii) to determine whether an association between the elastic properties of the *levator ani* and perineal clinical and B-mode ultrasound measures exists; and iii) to provide explorative data about an association between pelvic floor muscle characteristics and the risk of perineal tears.

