### Analysis

#### Judgment criteria

The primary judgment criteria will be the evolution of the shear modulus of the pelvic floor muscle (*levator ani* and external anal sphincter) across the pregnancy assessed at rest, during the Valsalva, and during a contraction.

Secondary judgment criteria will be:
the association between POP-Q measurements (especially gh and pb) and the elastic properties (shear modulus) of the levator ani muscle at each visit;the association between perineal B-mode ultrasound measurements and the elastic properties (shear modulus) of the levator ani muscle at each visit;the changes in shear modulus of the *biceps brachii* and *gastrocnemius medialis* muscles during pregnancy compared to the pelvic floor muscles;the association among the shear modulus of the pelvic floor muscles (*levator ani* and external anal sphincter) at the last visit, the mode of delivery (spontaneous vaginal delivery, operative vaginal delivery, cesarean delivery) and the potential occurrence of a perineal tear (RCOG-WHO classification, French guidelines) [35, 36].

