#### Plan of analysis

We will describe the anthropometric and sociodemographic characteristics of the included women. Age, BMI and term of pregnancy will be reported as the mean and standard deviation (SD). For all the other analysis, we will only consider data about women who completed the three planned visits. For each trimester, we will only collect continuous variables, which will be reported as the means and SDs. Changes in these variables during pregnancy will be investigated using a Friedman test. Obstetric data will be reported as the means and SD for continuous variables and as percentages and frequencies for categorical variables.

Regarding the study endpoints, we will first report the main outcome of this study, which consists of the changes in the pelvic floor muscle’s shear modulus across the pregnancy. Then, we will report the changes in all other measured pelvic floor-related parameters (POP-Q measurements, ultrasound B-mode measurements). We will look for an association between the shear modulus of the levator ani muscle and clinical (POP-Q measurements) and ultrasound B-mode assessments at each trimester using a Spearman correlation coefficient calculation. Second, we will report the changes in the shear modulus of the *biceps brachii* and *gastrocnemius medialis* muscles to look for changes between the different investigated locations. Third, we will look for an association between the shear modulus of the pelvic floor muscles (*levator ani* and external anal sphincter) and both the mode of delivery (vaginal or cesarean delivery) and perineal tear occurrence using univariate analysis. Variables with a level of significance greater than *p* < 0.15 in univariate analysis will be included in the multivariate analysis using a logistic regression. We will perform statistical analysis with Stata software (version V14IC; Stata Corporation, College Station, TX, USA). For all analyses, significance will be considered for *p* < 0.05, and we will calculate odds ratios (ORs) with 95% confidence intervals when appropriate.

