## Discussion

### Short summary of the study

It is difficult to predict the outcome of severe perineal trauma (OASI and/or levator avulsion) at childbirth, as there is a strong potential of an alteration of the woman’s health. One hypothesis to optimize the efficiency of risk prediction is to consider the intrinsic biomechanical characteristics of women’s pelvic floors. Such an approach may allow an individualized risk assessment personalized information for each woman. Our prospective, monocentric, longitudinal study will include 60 nulliparous pregnant women. Three visits are planned in this protocol (one per trimester of pregnancy) and will include clinical (POP-Q) and ultrasound assessment of the pelvic floor, SWE assessment of the pelvic floor muscles (*levator ani,* external anal sphincter) and the *biceps brachii* and *gastrocnemius medialis* muscles. Finally, data about the mode of delivery (cesarean section or vaginal delivery) and the occurrence of perineal tears will be collected. The main endpoint will be to describe the changes in the elastic properties of the pelvic floor muscles across pregnancy. The secondary endpoints will be to look for an association between SWE measurements of the *levator ani* muscle and clinical and ultrasound perineal assessments, to compare muscular changes during pregnancy among the pelvic floor muscles and the *biceps brachii and gastrocnemius medialis* muscles and to look for an association among the elastic properties of the pelvic floor muscles, the mode of delivery and the occurrence of perineal tears.

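### Secondary objective i compares change between pelvic floor and peripheral muscles, but the only test named for change works within one muscle and cannot make that comparison

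*Protocol article*

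**What the plan says.** The comparison is stated in three forms in the protocol article.

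- Background gives secondary objective i as "to look for specific changes of the pelvic floor muscles compared to peripheral muscles". The hypothesis just before it reads "They might be specific to pelvic floor muscles without, or less, significant changes for peripheral muscles such as" biceps brachii or gastrocnemius medialis.
- Judgment criteria lists change in the two peripheral "muscles during pregnancy compared to the pelvic floor muscles".
- Short summary of the study restates the endpoint as "to compare muscular changes during pregnancy among the pelvic floor muscles and the" two peripheral muscles.

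On method, the Plan of analysis states: "Changes in these variables during pregnancy will be investigated using a Friedman test". The Methods part of the abstract names the same test. For objective i, the Plan of analysis adds only that changes in biceps brachii and gastrocnemius medialis will be reported, in the "muscles to look for changes between the different investigated locations". It sets p < 0.05 for all analyses.

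**The concern.** A Friedman test applied to one muscle asks whether that muscle's shear modulus differs across the three visits. It says nothing about whether the pattern differs from that of another muscle. A significant result in levator ani beside a non-significant one in biceps brachii is not evidence that the two changes differ, because the second result may simply reflect lower power.

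The scale is also left open. The article's own resting values are far apart, so a side-by-side display of means in kPa could look like a pelvic-floor-specific rise even when the relative rise is the same. At stake is the claim that pregnancy acts specifically on the pelvic floor, for which the two peripheral muscles were added to every visit.

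**Working it through.** **Step 1. Objectives against methods.** The article disputes no figure here, so there is none to reproduce. Setting the aims beside the Plan of analysis:

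| Aim | Method named |
|---|---|
| Main: change in pelvic floor muscles | Friedman test |
| i: change compared with peripheral muscles | peripheral changes reported; no between-muscle test or estimate |
| ii: association with clinical and B-mode measures | Spearman coefficient |
| iii: association with delivery mode and tears | univariate analysis, then logistic regression |

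Only objective i lacks a method that matches its question.

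**Step 2. Why separate tests mislead.** Let two muscles have the same true change and let each test have power p. If the tests are independent, the chance that the first is significant and the second is not is p × (1 − p). This peaks at 0.5 × 0.5 = 0.25. At p = 0.54 it is 0.54 × 0.46 = 0.248.

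**Step 3. Simulation on the log scale.** Inputs from the article: three visits, alpha 0.05, and 60 × 0.80 = 48 completers (the stated aim is at least 50, and n = 50 gives similar results). Assumed, because the article gives no SDs: a linear rise over visits, identical in both muscles, and the within-woman log-SDs shown.

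| True rise in both | Log-SD levator / biceps | Levator significant, biceps not |
|---|---|---|
| 5% | 0.25 / 0.25 | 10% |
| 10% | 0.25 / 0.25 | 20% |
| 15% | 0.25 / 0.25 | 25% |
| 20% | 0.25 / 0.25 | 17% |
| 30% | 0.25 / 0.25 | about 2% |
| 15% | 0.15 / 0.15 | about 5% |
| 15% | 0.35 / 0.25 | about 14–15% |
| 15% | 0.50 / 0.25 | about 8–9% |
| 15% | 0.25 / 0.35 | about 35–36% |
| 15% | 0.25 / 0.50 | about 44–45% |

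When the levator is the noisier muscle, the reverse pattern (biceps significant, levator not) occurs in 36–45%. A paired contrast of the log changes gave a false difference in 4–6%.

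**Step 4. A second set of assumptions.** With n = 50, unit visit SD, equal change of 0.3 to 0.8 SD in both muscles and between-muscle error correlation of 0 to 0.5, the levator-only pattern occurred in 10–24% of studies. A direct muscle-by-visit test stayed at 4–5%. With a true difference (0.8 SD in one muscle, none in the other), that direct test had power of 54%, 71% and 85% at correlations of 0, 0.3 and 0.5.

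**Step 5. Scale.** Resting values in the article are about 16 kPa (levator ani), 3 kPa (biceps brachii) and 3.1 kPa (gastrocnemius medialis). The ratios are 16 / 3 = 5.3 and 16 / 3.1 = 5.2. An equal 20% rise is 0.20 × 16 = 3.2 kPa in levator ani and 0.20 × 3 = 0.6 kPa in biceps brachii.

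**The case against.** The article clearly intends a comparison, and only its technique is unnamed. A condensed article may leave that to a full protocol or SAP, neither of which is shown. This lowers the weight of the point but does not remove it: the article fixes a test for change, names a matching method for the other aims, and the test it fixes cannot answer this one.

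Four stronger readings are tempting, and the document does not support them.

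- *Specificity will be decided by comparing p-values.* No such rule is stated. It is an inference from the hypothesis wording in Background and the blanket 0.05 threshold.
- *False specificity would be the frequent result, at 35–45%.* Those rates need the biceps to be noisier than the levator. The article says elastography is reliable in the peripheral muscles and that no reproducibility data exist for the pelvic floor, so the opposite is at least as plausible. The error would then run mostly against the hypothesis.
- *The difference in resting level distorts the planned test.* The Friedman test uses within-woman ranks, so it does not. Scale matters only once changes are compared between muscles, and the gap depends on condition: stretched values are 35 and 19 kPa, a ratio of 1.8.
- *The objective cannot be answered.* It can. All four muscles are measured in the same women at each visit.

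The study also calls itself exploratory, with a descriptive main endpoint. That limits the severity, but the plan still applies p < 0.05 throughout.

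**Conclusion.** The gap is real. As written, the plan gives neither a valid test nor an estimate for secondary objective i. If separate p-values filled it, equal relative change would yield a levator-only result in roughly 2–25% of studies under equal noise, against about 5% for a direct contrast. Unequal noise moves the rate either way. These figures rest on assumed effect sizes and SDs; the structural point, that a within-muscle test cannot compare muscles, does not. The main outcome and data collection are unaffected. This should be fixed, but it is a moderate point.

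**What to change.** Add to the Plan of analysis, for each condition (rest, stretch, contraction), a within-woman comparison of the visit 3 minus visit 1 change in log shear modulus. Make it for levator ani and for external anal sphincter, since the article counts both as pelvic floor muscle, each against biceps brachii and against gastrocnemius medialis. Report each as a ratio of changes with 95% CI.

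A paired contrast is enough. If a mixed model with muscle × visit is preferred, include both woman and woman-by-muscle random effects. With a woman effect only, and women's levels assumed to differ by muscle (log-SD 0.3), the type I error of this contrast was 0.2% to 1.8%, so power is lost.

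State the log or relative scale in advance, base any statement of specificity on this contrast alone, and label it exploratory. With about 50 women its power may be moderate, so the interval should carry the interpretation. The cost is a few lines in the plan and a little analysis work.

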## Background

Perineal trauma is a frequent complication of childbirth, which may lead to several pelvic floor disorders, such as anal incontinence, urinary incontinence, pelvic organ prolapse and sexual dysfunction [1–4] In the most severe cases, perineal trauma could involve an obstetric anal sphincter injury (OASI) (rupture of the external anal sphincter and, worse still, opening of the rectal mucosae) and/or levator avulsion. OASI, which occurs in nearly 5% of first deliveries, is associated with postnatal anal incontinence and dyspareunia [1]. Levator avulsion, which occurs in nearly 10% of first deliveries, is associated with pelvic organ prolapse and sexual dysfunction [3]. These injuries are associated with trauma of the pelvic floor muscles at vaginal delivery during which these muscles are overstretched, up to three times their initial length [5]. Several risk factors are described in the literature (forceps delivery, fetal macrosomia, etc.) However, the occurrence of these complications remains very difficult to predict [1–4]. It is likely that the risk of pelvic floor trauma can be influenced by intrinsic characteristics of the pelvic floor muscles and their ability to lengthen sufficiently to enable passage of the fetus through the birth canal without being damaged. Identifying women with a high risk of perineal trauma antenatally would enable clinicians to propose individualized counseling and preventive strategies for these women.

Few studies have indicated that some intrinsic biomechanical characteristics of pregnant women could be associated with the risk of perineal trauma [6–8]. In a recent prospective study, we reported an association between peripheral ligamentous laxity (assessed at the metacarpophalangeal joint) and the risk of OASI. In that study, the women with the greatest ligamentous laxity had the greatest risk of OASI [8]. This result supports the hypothesis of an association between a woman’s individual biomechanical characteristics and her risk of perineal trauma. However, the main limitation of this study was that it was designed to analyze data about an upper limb joint, which is probably very different from pelvic floor muscle tissues [8].

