### Power calculation

This study deals with exploratory data with an absence of previous data that would allow a power calculation. Furthermore, the main endpoint of the project is descriptive (to describe changes in the elastic properties of the *levator ani* muscle during pregnancy), and, therefore, an a priori power calculation does not appear necessary. We aim to obtain and study the data from at least 50 women. We considered this sample size in part due to previous studies that reported an increase in *levator hiatus* area and ligamentous laxity during pregnancy, as well as changes in the intrinsic biomechanical characteristics of pregnant women, from between 20 to 50 women [17–19]. We estimate that 20% of the women will be excluded during pregnancy because of a complicated pregnancy and/or their own choice, leading to an objective of 60 inclusions.

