#### Preliminary data about the hypothetical association between elastic properties of women’s pelvic floors and obstetric perineal trauma

Finally, we will look for a potential association between the elastic properties of the pelvic floor muscles and the occurrence of perineal tears as well as the mode of delivery. Due to the expected number of women, it will not be possible to conclude about such an association. The objective is to provide preliminary data about the distribution of pelvic floor muscles elastic properties according the stage of perineal tear. We expect that these preliminary data would allow the future implementation of a larger multicentric prospective study investigating the interest of including the elastic properties of the pelvic floor muscles in our risk prediction of perineal trauma. This is required to offer each pregnant woman personalized information and an individualized preventive strategy. One prospect might be a selective use of episiotomy in high-risk women considering that this intervention, in a biomechanical study, reduce the stress on the muscles and the force required to delivery successfully [47]. Our data might be helpful in providing a justification for implementing this type of study and offering the possibility of performing a power calculation.

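### The p < 0.15 screen over six correlated shear moduli, followed by a multivariable logistic model at p < 0.05, asks more than about 48 women can support and gives estimates that ignore the selection

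*Protocol article*

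**What the plan says.** The Plan of analysis restricts everything beyond the baseline description to women who completed all three visits. It then relates the shear modulus of the levator ani and of the external anal sphincter to mode of delivery and to tear occurrence by univariate tests. The selection rule begins "Variables with a level of significance greater than" and gives the threshold as p < 0.15. Whatever is selected "in univariate analysis will be included in the multivariate analysis using a logistic regression". Significance is set at p < 0.05 for all analyses, with odds ratios and 95% intervals. The Abstract repeats the logistic model for tears.

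Under Judgment criteria, the primary criterion measures the modulus of both muscles at rest, during Valsalva and during contraction. The corresponding secondary criterion uses the last visit.

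The Power calculation section states "We aim to obtain and study the data from at least 50 women", then "We estimate that 20% of the women will be excluded during pregnancy", "leading to an objective of 60 inclusions".

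In the Discussion, the section on preliminary data about obstetric perineal trauma states "Due to the expected number of women, it will not be possible to conclude about such an association". It gives the purpose as preliminary data on how the moduli are distributed by tear stage.

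**The concern.** The rule is stated in the text, so this is not a detail left to a fuller document. It chooses variables by their relation to the outcome in a small sample, then refits them on the same women and reports p-values and intervals as if they had been chosen in advance. Odds ratios that survive such a screen tend to be too far from 1, and their intervals are too narrow. The candidates are repeated measurements of the same two muscles. When several pass, they compete in one model and their coefficients are hard to interpret.

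The wording of the threshold adds a smaller problem: a level greater than p < 0.15 can be read literally as keeping the variables that are not associated.

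The Discussion hopes that these data may help to justify and size a larger multicentre study. If the selected odds ratios were used for that, their optimism would be carried into its sample size.

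**Working it through.** **Inputs.** From the Power calculation section: 50 women wanted, 20% loss, 60 inclusions. From Judgment criteria: 2 muscles × 3 conditions = 6 moduli. From Plan of analysis: screen at 0.15, final test at 0.05, completers only. From Background: "OASI, which occurs in nearly 5% of first deliveries". Not in the protocol, hence assumed: any-tear rate 20% to 80%, cesarean rate 10% to 30%, correlation between moduli 0 to 0.6.

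**Women analysed.** The figure of 60 is reproduced by 50 × 1.20 = 60. Dividing instead gives 50 / 0.80 = 62.5, so 63. With 60 included and 20% lost, 60 × 0.80 = 48 remain.

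**Size of the smaller outcome class, all 48 women.**

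| Tear rate (assumed) | Smaller class | Parameters at 10 per parameter | At 5 per parameter |
|---|---|---|---|
| 20% or 80% | 48 × 0.2 = 9.6 | 1.0 | 1.9 |
| 30% or 70% | 48 × 0.3 = 14.4 | 1.4 | 2.9 |
| 50% | 48 × 0.5 = 24.0 | 2.4 | 4.8 |

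Six moduli exceed every entry, even on the looser rule.

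**Restricted to vaginal deliveries.** With 10% to 30% cesarean, 48 × 0.9 = 43.2 to 48 × 0.7 = 33.6 women remain. The smaller class is then at most 43.2 × 0.5 = 21.6 and, at a 20% or 80% tear rate with 30% cesarean, 33.6 × 0.2 = 6.7.

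**If the outcome were only anal sphincter injury (OASI).** 48 × 0.05 = 2.4 events expected. For a binomial with n = 48 and p = 0.05, P(0) = 0.95^48 = 0.085, P(0 or 1) = 0.30 and P(at most 4) = 0.91. No multivariable model could be fitted usefully.

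**Chance that the screen passes something when nothing is associated.** For six independent moduli, 1 − 0.85^6 = 0.62, with 6 × 0.15 = 0.9 expected to pass. The moduli are likely to be correlated, which lowers the 0.62. A null simulation (48 women, six equally correlated normal moduli and no other covariate, t-test screen at 0.15, then logistic regression on those selected) gave, at tear rates of 30% to 50%:

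| Correlation | At least one modulus passes | At least one final p < 0.05 |
|---|---|---|
| 0 | about 62% | about 22% |
| 0.3 | about 57% | about 14% |
| 0.6 | about 47% | about 5% |

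A separate run of the same kind put the first column at 46% to 63% and the second at 5% to 22%. At correlation 0.6 the final false-positive rate is close to nominal. This is because selected moduli that carry much the same information weaken each other in the joint model; it does not make the model sound.

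**Intrapartum items, conditionally.** The protocol also collects second-stage and expulsive-phase duration, epidural, mode of delivery, instrument and episiotomy, all arising after the last scan. If some entered the screen, the candidate list would lengthen. A null simulation with six correlated moduli and five further covariates gave at least one final p < 0.05 in 24% to 26% of studies at a 30% to 70% outcome. The model could also condition on consequences of muscle stiffness, since the protocol studies mode of delivery in relation to stiffness.

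**The case against.** The strongest reply is that this is a secondary analysis described as explorative, with its limits openly stated, and that screening at a relaxed p-value is common practice whose meaning readers will understand. Much of that stands. It limits the seriousness of the point, and the odd wording of the threshold is unlikely to mislead an analyst. It does not justify a method whose p-values and intervals are invalid after selection, when plain description would serve the stated purpose better.

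A reader might infer three stronger readings that the protocol does not support.

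- *The model rests on about two events.* That count belongs to OASI. The modelled outcomes are tear occurrence of unspecified grade and mode of delivery. For a tear rate of 30% to 70%, separation was essentially absent in simulation, so the model can be fitted, though with weak support.
- *The plan adjusts for intrapartum events.* No section says so. The sentence before the screening rule tests only the moduli, so its variables may be the moduli alone. The text neither admits nor excludes the delivery items.
- *The model contradicts the Discussion.* The objectives and the secondary criteria list an association, and the Discussion says it will be looked for. The two sit uneasily together but are not in flat contradiction.

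Nor does the protocol say that the selected odds ratios will feed the later power calculation. The distribution of moduli by tear stage could do that.

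**Conclusion.** The point holds for the model as written. About 48 women give a smaller outcome class of roughly 10 to 24 (tear rate 20% to 80% assumed), so one or two parameters at 10 events each against six correlated moduli. Excluding cesareans reduces this further. In 46% to 63% of studies with no true association, at least one modulus would pass the screen (tear rate 30% to 50%, correlation 0 to 0.6, both assumed), and 5% to 22% would end with a nominally significant odds ratio. These percentages depend on the correlation, which the protocol does not give. That estimates chosen by a screen are not corrected for it does not depend on any of these assumptions.

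The problem would be far worse if the outcome were restricted to OASI, and adjustment for consequences of stiffness would arise only if intrapartum items were admitted. The text states neither. The primary objective is unaffected. The change should be made because it costs little and brings the analysis into line with the purpose given in the Discussion.

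**What to change.** Delete the p < 0.15 screen and the data-driven multivariable model from the Plan of analysis, and the matching sentence from the Abstract. In their place:

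- Name the women at risk of a tear as those who deliver vaginally, and name the tear outcome.
- Report the last-visit modulus by tear grade, with mean, SD and a plot of individual values.
- Give one unadjusted odds ratio per SD, with 95% confidence interval, for the levator ani and one for the external anal sphincter, each in one condition named in advance. Use Firth's penalised likelihood or exact logistic regression if events are sparse.
- Label these results exploratory and make no significance claim.
- If an adjusted estimate is wanted, fix at most one or two covariates in advance from data already collected before delivery, such as age and BMI, and use no intrapartum events. Birth weight is not among the delivery data listed, so it is not available as the protocol stands.

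The cost is wording, and there is less analysis to do. What is lost is an adjusted multivariable model. That loss is small, because the protocol already says that this number of women cannot settle the association.
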